### 10.3 Populations for Analyses

All patients in each practice meeting inclusion criteria will be included in analyses, as practices (not patients) are the ones exposed to the intervention. The patient cohort to be analyzed for the primary endpoints (AWV utilization and composite preventive health services score) consists of patients:

- aged 50 and older
- have Medicare insurance
- have had at least 1 encounter in the past 12 months at a participating practice site
- are not deceased.

Multiple cohorts exist for our secondary endpoints, as these cohorts vary based on the preventive health service assessed. Cohorts for the secondary outcomes include those meeting the inclusion criteria for the primary outcomes who meet additional eligibility requirements for each preventive service listed in [Section 4.0](#_4_OBJECTIVES_AND) **Table 2**. We will use HEDIS and CMS metric specifications to specify inclusion and exclusion criteria for each preventive health service. As an example, the patient cohort for mammography includes the cohort for the primary outcomes who are female, aged 50 to 74, and do not meet HEDIS metric exclusion criteria.

### 10.4 Statistical Analyses

#### 10.4.1 General Approach

Descriptive statistics will be used to describe demographics of the primary patient cohort: age (means with standard deviations; range), gender (percentages), and race/ethnicity (percentages). For each practice and organization, we will summarize use of AWVs and preventive health services at baseline (Month 0) and every 6 months up to the end of the study (24 months after the completion of intervention implementation in the last set of practices). We will also use run charts to illustrate the monthly percentage of eligible patients who utilized AWVs and each preventive health service assessed ([Section 4.0](#_4_OBJECTIVES_AND) **Table 2**), as well as the composite preventive health services score.

**Linear mixed effects models** will be used to assess the effect of the intervention on the use of AWVs (primary endpoint), on the use of individual preventive health services (secondary endpoints), and on the composite preventive health services score (primary endpoint).

#### 10.4.2 Analysis of the Primary Endpoints

The primary endpoints are AWV utilization and the composite preventive health services score **(Table 6)**.

| **Table 6. Patient cohorts, primary endpoints, and timing of measurement** | | |
| --- | --- | --- |
| **Cohort** | **Endpoints** | **Time Frame** |
| Medicare patients aged 50+, with 1 or more visits in the past 12 months, not deceased | 1) ***AWV utilization*** (% of patients who completed an AWV or IPPE (CPT codes G0438, G0439, G0402)) within 12 months; 2) ***Composite preventive health services score*** (% of recommended services that are up to date) | Monthly |

***Primary objectives (examine effect of PT-AWV intervention on increasing AWVs and preventive health services utilization in diverse practice settings at 12, 18 and 24 months post-implementation)*:** we will use **linear mixed effects models** to assess the effect of the intervention on the use of AWVs and on the composite preventive health services score. These models account for correlation between repeated observations in the same cluster and the confounding effects of time and treatment. For example, with $Y_{ijt}$ as the indicator of AWV completion for patient i from cluster j at time t, the model is:

$Y_{ijt}=\mu+\alpha_{i}+\gamma_{j}{+ \beta}_{t}+X_{ijt}\theta+ Z_{ijt} + \varepsilon_{ijt}$,

where $\mu$ is the intercept,$\gamma_{i}$ and $\alpha_{j}$ are the random intercepts for subject i and cluster j with $\alpha_{j}\sim N\left( 0, \sigma_{\alpha}^{2} \right), \gamma_{j}\sim N\left( 0, \sigma_{\gamma}^{2} \right),$ $\beta_{t}$ is the fixed time effect, $X_{ijt}$ is the indicator of treatment mode for subject i cluster j at month t, $\theta$ represents the treatment effect, $Z_{ijt}$ is pre-specified patient and practice level covariate, and $\varepsilon_{ijt}$ is the residual with $\varepsilon_{ijt}\sim N\left( 0, \sigma_{\varepsilon}^{2} \right)$. We will approximate the secular time trend $\beta_{t}$ linearly in time with $\beta t$. Piece-wise constant time effect will be considered to accommodate possible non-linear time trends. This model will accommodate repeated patient visits and correlations within practices. All analyses will be carried out based on the intention to treat principle, which means that the treatment mode variable ($X_{ijt})$ is determined by the scheduled assignment of intervention implementation based on randomization, but not by the actual timing of implementation.

Given the probability of the treatment effect varying over time, we will consider the treatment effect, θ, as a function of post-intervention time, τ, such that $\theta=\theta(\tau)$. This is subsequently formulated as a random effect, with $\theta=\theta\left( \right)= \theta_{0}+\theta_{\tau}, \theta_{\tau}\sim N\left( 0, \sigma_{\theta}^{2} \right)$;[^163^](#_ENREF_163) in this case, $\theta_{\tau}$follows a normal distribution with mean zero and variance $\sigma_{\theta}^{2}$. We will apply Empirical Bayes estimates to assess the fluctuating treatment effect at various post-intervention times. We will estimate the probability of AWV completion between baseline and 12-months post-implementation, as well as between baseline and maintenance periods (18- and 24-months post-implementation, respectively).

Practices will have a heterogeneous composition of patient characteristics that have been associated with AWV and preventive services use. We will include these factors as covariates when comparing the change in AWV and preventive services use between pre- and post-intervention groups: age, gender, race (Asian, Black/African-American, White, Other), ethnicity (Hispanic, non-Hispanic), insurance coverage (fee-for-service Medicare, Medicare Advantage), and # of office visits per year. We will also include practice setting (community-based, academic, safety net), practice size, and percentage of racial/ethnic minority patients. We will also conduct subgroup analysis to examine heterogeneity of treatment effects by patient and practice characteristics, such as patient race/ethnicity, number of chronic conditions, and practice type (community-based, academic, safety net) on the effect of the intervention.

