### 5.3 Justification for Intervention

**Intervention Pilot-Testing.** The investigators successfully pilot-tested the PT-AWV intervention in an organization consisting of 3 practice sites.[^158^](#_ENREF_158) All practices used the eMDs EHR platform. As shown in **Figure 2**, AWV utilization in the past 12 months (across all sites) went from 7% at baseline to 54% eight months post-intervention implementation. Two larger practices each increased AWVs by about 40%, while the smallest practice doubled its AWVs (from 15% to 30%) before dropping to 21%.

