### 10.2 Sample Size Determination

In our pilot practices, the PT-AWV intervention increased AWVs from 8% at baseline to 54% eight months post-intervention in AWV-eligible patients (n=213, 576 and 639 patients at baseline in the 3 practices). Practices agreeing to participate in this project range in size from about 175-2700 eligible patients and have baseline AWV rates of about 16-45%, with most patients belonging to practices with rates under 35%. At the population level, we conservatively estimate our sample size to be a mean of about 1300 patients per practice. Behaviors of practices recruited from the same healthcare organizations may be correlated, so we will adjust power analyses using intra-class correlation (ICC). Based on our preliminary data, intra-class correlation for site was 0.03 and within subject correlation was -0.003 for AWV use one year apart. Since the stepped wedge design is relatively insensitive to ICC (because it is similar to a pre-test/post-test design), we conservatively estimate ICCs from .03 to .05 in our calculations and assume that ICC is mostly due to repeated patients seen in the same practice. Clinically meaningful increases would conservatively be 10% for all outcomes. The overall treatment effect is >99% for a 10% increase in AWVs and in the composite preventive health services score, based on a type-I error rate α = 0.05, 800-1300 patients per practice, and ICC=0.03 and 0.05 for 24 practices.

**Table 4** demonstrates power calculations to detect a meaningful treatment effect of 10% increase outcomes for a sample of 24 practices, with type-I error rate α = 0.05. We have >99% power to detect an overall improvement of 10% in AWV completion rates and the composite preventive health score in all scenarios from baseline to 12 months post-intervention.

| **Table 4. Power for treatment effect of 10% increase, type-I error rate α = 0.05, based on # monthly eligible patients and baseline rates of outcomes, and ICC for 24 practices** | | | |
| --- | --- | --- | --- |
| **Outcome / Mean # patients per site** | **Baseline rate, %** | **Power with ICC 0.05, %** | **Power with ICC 0.03, %** |
| ***AWV*** |  |  |  |
| 800 patients / practice | 10 | >99 | >99 |
|  | 30 | >99 | >99 |
|  | 50 | >99 | >99 |
| 1200 patients / practice | 10 | >99 | >99 |
|  | 30 | >99 | >99 |
|  | 50 | >99 | >99 |
| 1500 patients / practice | 10 | >99 | >99 |
|  | 30 | >99 | >99 |
|  | 50 | >99 | >99 |

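### For AWV utilization, the monthly model with patient and practice intercepts cannot represent overlapping 12-month windows, so its standard errors are 2 to 3 times too small even if practices never drift

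*Protocol*

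**What the plan says.** Protocol 10.4.2 defines AWV utilization as completion of an AWV or IPPE within 12 months, and Table 6 gives the time frame as monthly. The displayed equation has a patient intercept, a practice intercept, a time effect, a treatment effect, covariates and an independent normal residual. The treatment variable "is the indicator of treatment mode for subject i cluster j at month t", so the analysis unit is the patient-month. The section concludes: "This model will accommodate repeated patient visits and correlations within practices".

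The same section then lets the treatment effect vary with time since implementation as a random effect. That effect is indexed by exposure time only and is shared by all practices. The sensitivity-analysis paragraph calls the main analysis a mixed effects logistic regression, without adding a serial or practice-by-time term.

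Section 10.2 reports from the pilot that "within subject correlation was -0.003 for AWV use one year apart", and it states power "based on a type-I error rate α = 0.05, 800-1300 patients per practice, and ICC=0.03 and 0.05 for 24 practices".

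**The concern.** A patient intercept plus independent residuals implies the same within-patient correlation at one month, six months and three years. The look-back outcome behaves differently. Two consecutive monthly values are nearly the same measurement, and two values a year apart are, on the protocol's own figure, unrelated. The model therefore treats much of each month's repeated information as new.

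In addition, no term lets a practice drift over time relative to the others or respond differently to the intervention. With about 1300 patients per practice-month, any such variation would be read as precise information about treatment.

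At stake are the confidence interval and the type I error for a primary endpoint. The model form is also planned for the composite score, the individual services and the disparity analysis.

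**Working it through.** **1. The plan's own power figure.** Inputs from sections 5.1 and 10.2: 24 practices, 4 steps of 6, α = 0.05 (two-sided assumed), a gain of 10 percentage points, 800 to 1500 patients, baseline 10/30/50%, ICC 0.03 or 0.05. The protocol names no formula. I used the Hussey-Hughes variance with 5 periods:

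Var = Iσ²(σ²+Tτ²) / [(IU−W)σ² + (U²+ITU−TW−IV)τ²]

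Here I = 24, T = 5, U = 60, W = 1080 and V = 180, so IU−W = 360 and U²+ITU−TW−IV = 1080. In the least favourable cell (800 patients, 50%, ICC 0.03), σ² = 0.97×0.25/800 = 0.000303 and τ² = 0.03×0.25 = 0.0075. The SE is 0.58 points, and 10/0.58 is about 17 standard errors. All 18 AWV cells of Table 4 give power of essentially 100%, so the stated >99% reproduces.

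**2. Correlation implied by the outcome.** Windows k months apart share 12−k months. With AWV timing spread evenly over the year, the within-patient correlation is 1−k/12 up to 12 months and 0 after that. At k = 1 it is 11/12 = 0.92. At k = 12 it is 0, which agrees with the protocol's -0.003. The linear decline in between is an assumption.

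**3. Correlation the model can represent.** It allows one value at all lags. Averaged over all pairs of months, the true correlation is 0.20 (51 months) or 0.24 (42 months). The model therefore uses about 0.2 both where the truth is 0.92 and where it is 0.

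**4. Effect on the standard error.** Inputs: 24 practices × 1300 patients, 30% rate, closed cohort, linear model, steps 3 months apart, 39 months from first implementation, and 3 or 12 baseline months (assumed). I computed the generalized least squares SE under the plan's covariance, then the sandwich SE of the same estimator under the true covariance. Actual type I error = 2[1−Φ(1.96/ratio)]. Practices are held perfectly stable.

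| Baseline months | Time effect | Model SE (points) | True SE (points) | Ratio | Type I error |
|---|---|---|---|---|---|
| 12 | linear | 0.11–0.12 | 0.32 | 2.8 | 48% |
| 12 | monthly | 0.18 | 0.38–0.39 | 2.2 | 37% |
| 3 | linear | 0.12 | 0.31 | 2.6 | 45% |
| 3 | monthly | 0.17–0.18 | 0.39–0.40 | 2.3 | 39% |

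Ranges cover ICC 0.03 and 0.05; with stable practices the ratio does not depend on the ICC. Example: 1.96/2.78 = 0.705 and 2[1−Φ(0.705)] = 0.48. In the first row with ICC 0.05 (SEs 0.114 and 0.318), the reported 95% half-width would be 1.96×0.114 = 0.22 points, where 1.96×0.318 = 0.62 is needed.

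Simulation agrees. With 600 null trials of practice-month means (12 baseline months), rejection was 48% (linear) and 38% (monthly). A patient-level simulation with 300 patients per practice and 300 runs gave 45% and 32%.

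**5. Adding the random effect over exposure time.** In the 600-trial simulation the rates stayed at 48% and 38% with stable practices. With drift (ICC and year-apart correlation of 0.03 and 0.95, or 0.05 and 0.90) they were 63% to 76%.

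**6. Adding practice drift.** If practice effects in non-overlapping years correlate 0.95 to 0.80 instead of 1, the type I error is roughly 60% to 87%, depending on ICC, time effect and how the drift is modelled. The protocol gives no value, so this range is an assumption.

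**7. Power with the true standard error.** In the worst case of step 6 under the formula of step 4 (correlation 0.80, ICC 0.05, 3 baseline months, monthly effects), the true SE is 1.50 points. A 10-point effect is 10/1.50 = 6.7 standard errors, so power stays above 99%.

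**The case against.** **The equation is only an example, and the SAP may add robust variance.** The equation is introduced as an example, and variance estimators are often left to a SAP, which is not at hand. But this protocol writes out the covariance structure and says that it suffices. That statement is wrong whatever the SAP adds.

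**The absolute error is small.** This stands. Overlap alone moves the SE from 0.11–0.18 to 0.31–0.40 points, against "Clinically meaningful increases would conservatively be 10% for all outcomes". A genuine 10-point finding would not reverse.

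**A reader might infer that the power tables are wrong.** The documents do not support that. The >99% reproduces, survives moderate practice drift, and rests on a covariance model that section 10.2 does not name. The temptation comes from the uneven pilot response: "Two larger practices each increased AWVs by about 40%, while the smallest practice doubled its AWVs (from 15% to 30%) before dropping to 21"%. Gains of 40, 40 and 15 (or 6) points have an SD of 14.4 (or 19.6). Carried unscaled to a 10-point effect, an SD of 15 gives SE 15/√24 = 3.1 and power 88%, and an SD of 20 gives 65%. But those SDs come from three practices with mean gains of 31.7 (or 28.7) points. Scaled to a 10-point mean, they are 14.4×10/31.7 = 4.5 and 19.6×10/28.7 = 6.8, and power stays above 99%.

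**A reader might extend the same inflation to every endpoint.** It was computed only for AWV. Tetanus and colonoscopy have windows of about ten years, and hepatitis C screening is once only. Status on these persists, so a patient intercept may fit much better. In the disparity interaction, drift common to racial groups largely cancels. The logistic version of the model was not computed either.

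**Conclusion.** The statement that the model accommodates repeated visits and within-practice correlation is wrong for monthly AWV utilization. Window overlap alone makes the model standard error 2.2 to 2.8 times too small, and a nominal 5% test rejects a true null in about 37% to 48% of trials. This follows from the 12-month window and the protocol's year-apart correlation. It assumes linear decay between those two points, a closed cohort, a 30% rate, the linear model, and practices that do not drift. Any practice-by-time variation makes it worse, by an amount that the documents do not fix. The random effect over exposure time does not remove it.

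The consequence is intervals that are too narrow and false positives for small effects, such as effects in the maintenance period or in subgroups. It does not make the trial too small for a 10-point gain. The composite, the individual services and the disparity analysis share the model form and should be checked, but no size is claimed for them.

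**What to change.** In section 10.4.2:

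- Base primary inference on the 24 practices: a practice-clustered (sandwich) variance with a small-sample correction, a permutation test over the stratified randomization of section 7.3, or both.
- Add practice-by-period and practice-by-treatment random effects as a supplement, not as the sole remedy. Under overlap alone the practice-by-period variance is estimated at zero and the type I error stays at 48% and 37%. Adding practice-by-treatment still leaves about 14%. Kenward-Roger does not correct a misspecified residual covariance.
- Delete the sentence on accommodating repeated visits, or qualify it by naming the variance estimator that makes it true.
- Optionally add a sensitivity analysis with non-overlapping windows, for example AWV completed in the quarter. This changes the outcome from the defined primary endpoint, so it belongs in a sensitivity analysis.

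The cost is wider intervals and a little more analysis work. No new data are needed, and the power tables need not be withdrawn.

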***Sensitivity analysis.***

Our main analysis will be a mixed effects logistic regression model with a linear secular time trend. As a sensitivity analysis, we will also explore a piece-wise constant time trend to accommodate a potential non-linear time trend. In addition, we will examine possible time-treatment interaction, to see if the treatment effect increases or decreases over time.

***Secondary objective (examine effect of PT-AWV intervention on reducing racial/ethnic disparities in AWV utilization)***: For each practice and organization, we will summarize use of AWVs by patient race/ethnicity at baseline and every 6 months (up until month 48 of the study) using descriptive statistics. We will also use run charts to illustrate and compare monthly AWV utilization by patient race/ethnicity. **Linear mixed effects models** will be used to directly estimate the percentage change in AWVs and in disparity reduction. The primary covariates in these models are race (Asian, Black/African-American, White, Other) and ethnicity. These models will include fixed effects of treatment, time, treatment-race/ethnicity interaction and patient and practice-level covariates. Other covariates will include: age; gender; insurance coverage (fee-for-service Medicare, Medicare Advantage); # of office visits per year; and practice setting, size, and % of racial/ethnic minority patients. Patients and practices are considered as random effects and piece-wise constant time effect will be constructed to compare the racial/ethnicity disparities in AWV use before and after the intervention, based on the estimates of fixed effects.

***Missing data.*** Mixed effects models accommodate the imbalance of patient data, assuming that they are missing at random. Based on our preliminary data, we expect few missing data for patient age, gender, insurance and number of office visits per year. For missing data on race, we will perform analyses with missing race as a variable and also will impute the race/ethnicity variable.

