### 7.2 Fidelity

#### 7.2.1 Interventionist Training and Tracking

Variability of intervention implementation is expected because the intervention will be tailored by site. We will track dates of completion of meetings and trainings.

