| ***Composite preventive health score*** |  | >99 | >99 |
| 800 patients / practice |  | >99 | >99 |
| 1200 patients / practice |  | >99 | >99 |
| 1500 patients / practice |  | >99 | >99 |

Our pilot data suggested a decrease in ***racial/ethnic disparities*** in AWV utilization: at baseline, 7.7% of White patients and 4.9% of non-Whites completed AWVs (p=0.09), whereas 6 months post-implementation, 49.8% of White patients and 50.5% of non-Whites completed AWVs (p=0.63).

**Table 5** demonstrates power calculations to detect a 5% reduction in racial/ethnic disparities for AWVs with a sample of 24 practices, ICC=0.05 and type-I error rate α = 0.05. We will have >99% power to detect a 5% reduction in racial/ethnic disparities in AWVs between White and Hispanic patients and >99% power to detect a 5% reduction in disparities between White and Black patients for AWV completion. This calculation assumes the intervention effect is about 10% for White patients and 15% for Black and Hispanic patients, and that about 60%, 20% and 15% of the study population are White, Hispanic, and Black. For the composite preventive health services score power calculation, we further assume that on average each patient is eligible for > 8 preventive health services.

| **Table 5. Power for detecting 5% reduction in racial/ethnic disparities for AWVs and composite preventive health services score, with a type-I error rate α = 0.05 and ICC=0.05, based on patients/practice and baseline rates of outcomes** | | | | |
| --- | --- | --- | --- | --- |
| **Outcome** | **Baseline rate, %** | **Baseline rate, %** | **Power for Black-White disparity reduction, %** | **Power for Hispanic-White disparity reduction, %** |
| ***AWV*** | ***White*** | ***Black/Hispanic*** |  |  |
| 800 patients / practice | 30 | 10 | >99% | >99% |
|  |  | 15 | >99% | >99% |
|  |  | 20 | >99% | >99% |
|  | 40 | 10 | >99% | >99% |
|  |  | 15 | >99% | >99% |
|  |  | 20 | >99% | >99% |
|  | 50 | 10 | >99% | >99% |
|  |  | 15 | >99% | >99% |
|  |  | 20 | >99% | >99% |
| 1200 patients / practice | 30 | 10 | >99% | >99% |
|  |  | 15 | >99% | >99% |
|  |  | 20 | >99% | >99% |
|  | 40 | 10 | >99% | >99% |
|  |  | 15 | >99% | >99% |
|  |  | 20 | >99% | >99% |
|  | 50 | 10 | >99% | >99% |
|  |  | 15 | >99% | >99% |
|  |  | 20 | >99% | >99% |
| 1500 patients / practice | 30 | 10 | >99% | >99% |
|  |  | 15 | >99% | >99% |
|  |  | 20 | >99% | >99% |
|  | 40 | 10 | >99% | >99% |
|  |  | 15 | >99% | >99% |

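### The disparity model lets no treatment effect vary by practice, so its treatment-by-race/ethnicity test can be anti-conservative for inference beyond these 24 practices or about equity within practices

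*Protocol*

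**What the plan says.** The disparity model is described in protocol section 10.4.2, in the paragraph on the secondary objective. Its fixed part is: "These models will include fixed effects of treatment, time, treatment-race/ethnicity interaction and patient and practice-level covariates". Its random part is: "Patients and practices are considered as random effects". Earlier in section 10.4.2 the model for the primary endpoints defines these random effects as intercepts for subject and cluster. Practice setting, practice size and percentage of minority patients are listed as covariates, with no stated interaction with treatment. The one random treatment effect in the plan is indexed by time since the intervention and shared by all practices: "we will consider the treatment effect, θ, as a function of post-intervention time, τ".

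Elsewhere the protocol says that practices will differ:

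- Section 7.2.1 on delivery: "Variability of intervention implementation is expected because the intervention will be tailored by site".
- Section 5.3 on the pilot: "Two larger practices each increased AWVs by about 40%, while the smallest practice doubled its AWVs (from 15% to 30%) before dropping to 21" percent.
- Section 10.4.2 expects patient composition to be heterogeneous across practices, and section 5.1 spreads the sample over 8 community, 8 academic and 8 safety net practices.

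Table 5 in section 10.2 gives power above 99% in every row for a 5-point disparity reduction, with "ICC=0.05 and type-I error rate α = 0.05". No allowance for a treatment effect that varies by practice is mentioned.

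**The concern.** The intervention acts on whole practices. Suppose a practice with many Black or Hispanic patients responds strongly, and its White patients gain just as much. A model with one shared treatment effect cannot credit the gain to the practice. Part of it goes to the treatment-by-race/ethnicity coefficient, because minority patients are over-represented there. A high-minority practice that responds poorly pushes the coefficient the other way. There are only 24 such practice-level deviations, but the stated model treats the resulting movement as patient-level noise over thousands of patients.

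At stake is the secondary objective. A few practices implementing well or badly could produce a claim of reduced disparity, or of widened disparity, when patients of different race or ethnicity in the same practice benefited equally. The random practice intercept does not absorb this, because it covers differences in level and not in response. The percentage of minority patients as a main-effect covariate does not absorb it either.

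**Working it through.** **Inputs from the protocol.** 24 practices, 4 steps of 6 (section 5.1). Mean 1300 patients per practice, range 175 to 2700; within-subject correlation -0.003, so patient intercept variance was set to 0 (section 10.2). ICC and alpha as quoted above, with alpha taken as two-sided. For the target: "This calculation assumes the intervention effect is about 10% for White patients and 15% for Black and Hispanic patients", which is a 5-point interaction. For the mix: "about 60%, 20% and 15% of the study population are White, Hispanic, and Black".

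**Assumed, because the protocol does not give them.** The between-practice SD of the effect (s), and the between-practice spread of racial mix. The only evidence on s is the three pilot practices, reading the stated gains as percentage points:

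- 40, 40, 15: mean 31.7, SD 14.4
- 40, 40, 6 (after the fall to 21%): mean 28.7, SD 19.6
- Scaled to a 10-point mean effect: 10 × 14.4/31.7 = 4.6 and 10 × 19.6/28.7 = 6.8

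A range of 5 to 15 points for s was therefore used.

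**The plan's own figures.** Using the Hussey-Hughes stepped-wedge variance with 5 periods, Table 4 reproduces: power is above 99.9% in all rows. For Table 5, generalised least squares (GLS) on practice-by-period-by-race cells with a random practice intercept gives 99.98% (Black-White) and 99.999% (Hispanic-White) at 800 patients per practice. This counts the patients in each period, as the monthly wording of the Table 4 title implies. If they were split over 5 periods, power would be 69% to 96%.

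**Formula for the concern.** For practice j let V0 be the covariance under the stated model (random intercept only) and V = V0 + s²xx′ the covariance when the effect varies by practice, where x is the treatment indicator. With A = ΣX′V0⁻¹X:

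- model-based variance: A⁻¹
- true variance: A⁻¹(ΣX′V0⁻¹V V0⁻¹X)A⁻¹
- rejection rate at nominal 5%: 2[1 − Φ(1.96 × SE_model / SD_true)]

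No practice has any racial difference in effect, and percentage minority is in the model as a main effect.

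One worked case, with White share SD 13.9 points and s = 10: SE_model = 0.68 and SD_true = 1.52 points. Then 1.96 × 0.68/1.52 = 0.88, and 2[1 − Φ(0.88)] = 0.38. The unrounded results are 37% (Black) and 40% (Hispanic).

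**Results.** Rejection rates in percent, Hispanic/Black, 1300 patients per practice, 5 periods:

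| Differences in mix between practices | s = 5 | s = 10 | s = 15 |
| --- | --- | --- | --- |
| None | 5.0/5.0 | 5.0/5.0 | 5.0/5.0 |
| White share SD 5 points | 6.2/6.4 | 9.9/10.8 | 15.7/17.5 |
| White share SD 8 points | 9.5/9.2 | 21/21 | 34/33 |
| White share 72/68/40% by organisation (SD 14) | 15/12 | 36/29 | 51/44 |
| Organisation plus practice differences (SD 16) | 18/16 | 41/37 | 56/53 |

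A separate GLS calculation for Black versus White patients only gave 11/25/40% for s = 5/10/15 when the Black share of the two groups was 12/16/32% by setting, and 25/51/65% when it was 6/10/44%.

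**Check by simulation.** Binary outcomes, practice sizes 175 to 2700, REML variances, 400 runs per scenario, simulation error about 2 points. The planned model rejected in 8.0/4.5% with no planned difference in mix (s = 10), 40/27% with organisations differing (s = 10), 43/37% with both sources of difference (s = 10) and 60/56% (both, s = 15).

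**With a random practice-level treatment effect added.** In the same simulations rejection was 3 to 7% in all seven scenarios. In the GLS calculation the interaction SE rose at most from about 0.67 to 0.72 points. Power for 5 points is then Φ(5/0.72 − 1.96) = Φ(4.98), above 99%. At 800 patients the SE scales to 0.72 × √(1300/800) = 0.92, and Φ(5/0.92 − 1.96) = Φ(3.5), still above 99%.

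**The case against.** The strongest objection is that a false positive depends on the question asked. The protocol states the objective as reducing disparities in use of the visit, and does not restrict it to differences within practices. If high-minority practices respond better, the pooled gap really does narrow. In a pre/post simulation (600 runs, 1300 patients per practice) the planned test rejected zero in 7/16/28% of runs (moderate segregation) and 16/36/54% (stronger) for s = 5/10/15. Tested instead against the true change in the pooled Black-White gap in those same 24 practices, it rejected in only 4/4/4% and 3/3/5%. This stands. A reader might infer that the interval is too narrow whatever the question, but for the pooled change in these practices alone it is not.

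Second, the size is not known. A reader might infer that the test rejects far more than 5% as a matter of course. The documents do not support that, because they give neither spread. Scaled to a 10-point mean, the pilot points to an s of about 5 to 7. Values of 10 and 15 around a mean of 10 imply, under a normal distribution, a negative effect in Φ(−1) = 16% and Φ(−0.67) = 25% of practices. This stands as a limit on the upper figures.

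Third, the intercept-only form is introduced as an example for the primary endpoints, and an analysis plan not shown could add slopes. This carries less weight: the disparity paragraph lists its own terms, and none lets the effect vary by practice.

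Fourth, the summaries and run charts by race/ethnicity, and the planned heterogeneity analyses, might reveal the pattern. They do not correct the standard error.

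A reader might also infer a known direction of bias, since section 3.2 reports low adoption in practices serving underserved patients. That concerns adoption without the intervention. The protocol has no data on response to it by minority share.

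**Conclusion.** The point holds in conditional form. As stated, the disparity model omits between-practice variation in the treatment effect, while the protocol expects the effect and the patient mix both to vary. For inference to other practices, or about equity within practices, the standard error of the treatment-by-race/ethnicity coefficient is then too small.

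Both kinds of variation are needed. With equal racial mix there is no inflation. With an effect SD of 5 points and small to moderate differences in mix, the false-positive rate is about 6 to 11%. With effect SDs of 10 to 15 points and moderate to large differences in mix, it is roughly 20 to 60%. Both spreads are assumed ranges. The results are for the linear model named for this objective; the logistic model that section 10.4.2 also mentions was not run.

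This is worth correcting because the objective is a headline one and the correction is cheap. It does not show that the planned test will fail.

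**What to change.** In the secondary-objective paragraph of section 10.4.2:

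1. Add a random practice-level treatment effect (a random slope for treatment by practice) to the disparity model.
2. As a check, report cluster-robust standard errors with a small-sample correction for 24 practices. This option was not simulated here.
3. State whether the disparity contrast is within-practice or overall, and whether it is meant to generalise beyond the 24 practices.
4. Report whether higher-minority practices gained more as a separate practice-level estimate, so that the between-practice part of any change in the gap is kept.

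Practice-by-month effects are not required. They add many parameters with monthly data and would remove the between-practice part from the test.

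The cost is a change of wording, a slightly larger model and the marginally wider interval shown in the working. No new data are needed, and the power claim in Table 5 for a 5-point reduction survives if patients are counted per practice per period.
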